## Abstract

**Background:**

CanRisk is a risk assessment tool that implements the BOADICEA multifactorial breast cancer risk model. The BOADICEA model is recommended for use by the National Institute for Health and Care Excellence (NICE) in English, Welsh, and Northern Irish secondary/tertiary care to identify women who may be at moderate or high risk of developing breast cancer. BOADICEA combines information on cancer family history, demographic, lifestyle, hormonal risk factors and mammographic density with polygenic scores (PGS). Offering risk assessment using CanRisk in general practice has the potential to identify more women at moderate or high risk of developing breast cancer and improve their management and the appropriateness of referrals to secondary/tertiary care.

**Materials and methods:**

In this feasibility study we plan to invite women aged 40–49 years from 5–8 practices across Cambridgeshire and Peterborough in England, UK to complete a breast cancer risk assessment using CanRisk via a newly developed public-facing version of the CanRisk tool and provide saliva samples for PGS. The study team will provide a risk report back to both the participants and their GP, with those women at above-population level risk advised to make an appointment with their GP to be referred to the clinical genetics service and subsequently managed in line with current NICE guidelines. This study will provide evidence on (1) whether offering cancer risk assessment including PGS in general practice is feasible and acceptable to women and healthcare professionals; (2) whether this approach can identify women at above-population level risk of breast cancer who would otherwise not have been identified and so not had access to risk-reducing options; and (3) the costs associated with implementing proactive multifactorial breast cancer risk assessment in women under 50 within general practice.

**Study registration number:**

This study is listed on the ISRCTN registry. The registration number is ISRCTN17376192.

## Introduction

CanRisk is a cancer risk prediction tool that implements the Breast and Ovarian Analysis of Disease Incidence and Carrier Estimation Algorithm (BOADICEA) multifactorial model. This validated model combines information on family history, demographic, lifestyle, and hormonal risk factors, rare pathogenic genetic variants in cancer susceptibility genes, common genetic susceptibility variants summarised as a polygenic score (PGS), and mammographic density to estimate an individual’s future risk of developing breast cancer and of carrying a pathogenic variant in breast/ovarian cancer susceptibility genes [1–4]. CanRisk is regulated as an invitro diagnostic medical device in the UK and carries CE and UKCA markings. The National Institute for Health and Care Excellence (NICE) recommends BOADICEA and endorses CanRisk as a tool for assessing breast and ovarian cancer risk [5,6]. Depending on the degree of risk, women at above-population level risk are then potentially eligible for additional breast screening or risk-reducing medication [7].

Much research is being done to identify women over 50 years old who are at above-population level risk through the national breast cancer screening programme [8,9]. However, current guidance is that the selection of women under 50 years who should be referred for a risk assessment in secondary/tertiary care should be based on family history alone. This misses up to half of women who are at above-population level risk based on multifactorial risk assessment [10].

In June 2022, NICE also updated the guidelines on familial breast and ovarian cancer removing the recommendation against proactive assessment of breast cancer risk in general practice. This change was supported by a stakeholder consultation and opens up the potential for a general practice-based screening programme to identify those at above-population level risk of breast cancer rather than requiring women to self-present with concerns. This approach misses most women estimated to be at higher risk and increases inequalities [11]. A review of the literature against the consolidated framework for screening found that proactive risk assessment in general practice currently satisfies many of the standard principles for screening for women under 50 years [12]. However, while studies have demonstrated general acceptability (according to Sekhon et al [13]) and enthusiasm for assessing risk within general practice, previous research with the CanRisk tool has highlighted the need to tailor its development and use to the specific needs of general practice [14]. Research has also identified potential challenges to implementation, including the time needed to complete the assessment, IT requirements, competing demands and priorities, and training of staff [15]. It is not known whether multifactorial risk assessment will be acceptable to women within general practice or what the expected uptake would be and, despite rapid advances in understanding of the PGS contribution to risk assessment, few studies have attempted to implement PGS analysis within a general practice setting.

## Aims and objectives

The overall aims of this study are to evaluate the feasibility, acceptability and psychological impact of proactively offering multifactorial breast cancer risk assessment incorporating PGS using CanRisk in general practice, and to collect estimates of outcomes and data on costs and healthcare utilisation. The latter will inform the design of a future trial and a health economic analysis to model the estimated reductions in breast cancer incidence and mortality if proactive breast cancer risk assessment using CanRisk were to be introduced in general practice across the UK.

Specific objectives:

To quantify uptake of proactive multifactorial breast cancer risk assessment using CanRisk in general practice amongst women under 50;To assess the acceptability of all stages of proactive multifactorial breast cancer risk assessment using CanRisk within general practice from the perspective of women, GPs, and staff in General Practice.To compare the number of women identified as at moderate or high risk of breast cancer following proactive multifactorial breast cancer risk assessment with those identified through routine care and the number expected from population-based studies;To quantify the psychological and behavioural impact of proactive multifactorial breast cancer risk assessment using CanRisk in general practice amongst women;To quantify the amount of data collected via the MyCanRisk public-facing data collection tool within a general practice population;To estimate the distribution of breast cancer risk amongst women under age 50 taking up the opportunity for multifactorial risk assessment following proactive invitation and uptake of risk-reducing interventions amongst those at moderate or high risk to inform sample size calculations for the design of a future randomised controlled trial;To estimate differences in uptake of proactive multifactorial breast cancer risk assessment and breast cancer risk distribution of women between general practices to inform the design and sample size calculations for a future cluster-randomised controlled trial;To collect data to enable estimation of the cost of delivering proactive multifactorial breast cancer risk assessment using CanRisk within general practice.

## Materials and methods

### Ethical considerations

REC approval from the Ethical and Health Research Authority has been granted by East of England – Cambridge Central Research Ethics Committee (REC reference 23/EE/0199).

Cambridge University Hospitals NHS Foundation Trust and the University of Cambridge are joint sponsors for this study.

Cambridge University Hospitals NHS Foundation Trust, as a member of the NHS Clinical Negligence Scheme for Trusts, will accept full financial liability for harm caused to participants in the study through the negligence of its employees and honorary contract holders. There are no specific arrangements for compensation should a participant be harmed through participation in the study, where no-one has acted negligently. The University of Cambridge will arrange insurance for negligent harm caused as a result of protocol design and for non-negligent harm arising through participation in the study.

### Design and setting

The study is a pragmatic multicentre feasibility study taking place in 5–8 GP practices in Cambridgeshire and Peterborough, England, UK. Fig 1 shows the study schedule (SPIRIT).

**Fig 1 pone.0336902.g001:**
[figure not shown]
Study schedule of enrollment, interventions, and assessments according to SPIRIT 2013 requirements.

### Participants

The target population is women aged 40–49 years. The upper limit age of 49 years has been chosen as all women in England are invited to participate in the national breast cancer screening programme at age 50, and several studies are already in progress to evaluate the potential for offering risk assessment alongside mammography to identify women at above population risk [8,9,16].

An initial lower limit of age 40 years has been chosen because the main intervention amongst women at moderate and high risk of breast cancer is enhanced breast screening, and 40 is the minimum age in Cambridgeshire and Peterborough where women at moderate risk are eligible for this. If recruitment into the study is lower than expected, reducing the minimum recruitment age to 35 will be considered.

To be eligible for the study, women must also be registered with a participating general practice; and have capacity to consent and understand English.

Women are not eligible for the study if they have a breast cancer susceptibility gene already identified in their family or an entry in their medical records indicating any of: a personal history of breast or ovarian cancer, a known germline pathogenic variant in a breast cancer susceptibility gene, a previous diagnosis of metastatic cancer or entry on the palliative care register, or prior notification of dissent to research.

### Processes and interventions

#### Practice recruitment.

GP practice recruitment was supported by the Clinical Research Network (CRN) Eastern. They approached practices across Cambridgeshire and Peterborough that refer patients at increased risk of developing breast cancer to the clinical genetics service at the Cambridge University Hospital NHS Foundation Trust. Practices were recruited from different areas to maximise participant sociodemographic and ethnic diversity. Practices that agree to take part signed a practice agreement form. Reasons for practices declining to take part in the study were collected where possible.

#### Participant recruitment.

Eligible women are identified through searches of the electronic health records at General Practices based on the inclusion and exclusion criteria above. To prevent including women who may reach the age of 50 years between the searches being completed and receiving the invitations (see ‘Processes and Interventions’ section below), the search includes women aged 40–48 years. Depending on the population size of each practice, recruitment rate, and overall uptake into the study, either all or a random sample of those women who meet the eligibility criteria are invited to take part in the study. Invitations are staggered in random order. Those women are sent an invitation letter and S3 Participant information sheet by post. A reminder letter is sent by post two to four weeks later to those women who have not completed the consent form.

Women can complete the online written consent form which includes a screening question about breast cancer susceptibility gene already identified within their family. Those answering yes to this screening question are advised to make an appointment to discuss their breast cancer risk with their GP and are not able to continue with the study. After providing online written consent, all participants are asked to complete a short baseline questionnaire (details below) hosted online. On completion of the baseline questionnaire, participants are asked to provide data for a breast cancer risk assessment.

Recruitment opened on the 28^th^ of November 2024 for a duration of 8 months (until the 30^th^ of June 2025) or until 1,000 women have been recruited, whichever happens first.

Participant recruitment and flow through the study is summarised in Fig 2.

**Fig 2 pone.0336902.g002:**
[figure not shown]
Study processes.

#### Breast cancer risk assessment.

Personalised risk estimates are generated using the CanRisk tool. Population-based studies have shown that BOADICEA, including incorporation of polygenic scores, has moderate-to-good discrimination with AUCs or c-indices of 0.68–0.69 in women aged less than 50 years or those who are premenopausal [3,17] and is well calibrated with a ratio of expected to observed number of cases (E/O) of 0.97 [17].

For this study, personalised risk estimates are calculated based on family history, demographic, lifestyle and hormonal factors in addition to a PGS based on 309 common genetic variants [18]. Data on family history, lifestyle and hormonal factors is collected via the MyCanRisk app. Women receive a link to the MyCanRisk app after completing the consent and baseline questionnaire. MyCanRisk is a platform independent Progressive Web App that supports the on- and off-line collection of personal risk factor information alongside the detailed family history required to conduct a CanRisk calculation.

Participants have the option not to have PGS testing. For those participants consenting to this element of the study receive a saliva sampling kit on the post. The returned kits are collated by the research team and sent in batches for analysis by a clinically accredited laboratory. DNA samples which pass quality control are genotyped using a genome-wide array, specifically the Illumina Global Screening v4 Array (GSAv4). These data are then used (in conjunction with imputation to a reference panel to estimate genotypes for SNPs not on the array) to compute the 309 SNP PGS. The data is then sent to the bioinformatics provider for PGS analysis. The data is also used to estimate genetic ancestry: this enables the PGS to be standardised to the appropriate population and the use of ethnicity-specific BOADICEA model within CanRisk [19]. These results will then be returned to the research team.

The research team incorporates the PGS results together with the data on family history, lifestyle and hormonal factors collected via MyCanRisk, into the CanRisk tool and generate a personalised risk estimate for each participant. For those women opting not to have PGS testing, the personalised risk estimate is based on family history, lifestyle and hormonal factors only.

#### Risk categorisation and returning risk assessment results.

Based on the CanRisk breast cancer risk estimate and current NICE guidelines [7], participants are categorised into one of three risk groups: near population level risk, near population level risk but with additional features in the family history (i.e., sarcoma in relative < 45 years; glioma or childhood adrenal cortical carcinomas; complicated patterns of multiple cancers at a young age; Jewish ancestry), and moderate or high risk.

Women with an estimated breast cancer risk in the near population level risk group and without any additional risk factors based on their family history (see Table 1) receive a letter from the study team informing them that they are at near population level risk for breast cancer along with a breast awareness leaflet and the risk output from the CanRisk tool. The breast awareness leaflet is in line with current NICE guidance covering all the required fields (i.e., 5-point NHS plan for being breast aware, when to examine your breasts, what to look for, changes to look for, lifestyle advice, and further information). A copy of both the letter and risk output is also sent to the participants’ GP. Women with an estimated risk at near population level but with additional risk factors within their family history and those at moderate or high risk receive a results letter informing them that they may be at above average population level risk for breast cancer and advise them to make an appointment to discuss with their GP. They are also sent the breast awareness leaflet, and a copy of both the letter and risk output is sent to the participants’ GP. The GP or a delegate practice staff member adds the appropriate codes to the medical records for all participants.

**Table 1 pone.0336902.t001:** Risk categorisation.

Risk	Near population risk	Moderate risk	High risk
Lifetime risk between ages 20 and 80	<17%	≥17% - < 30%	≥30%
Risk between ages 40 and 50	<3%	≥3% - < 8%	≥8%

Women confirmed to have additional risk factors based on their family history or those at estimated moderate or high risk for breast cancer are offered referral to the regional clinical genetics service using a specially designed referral proforma. Women referred to the regional clinical genetics service are then managed in line with current practice.

Table 1 shows the risk cut offs for near population risk, moderate risk and high risk for lifetime risk (defined as the risk between the ages of 20 and 80), and 10 year risk between the ages of 40 and 50.[7] For women falling in different categories based on the two definitions of risk, whichever is highest determines the risk category (i.e., near population risk, moderate and high risk) they will be classified as for the purposes of implementing current NICE guideline [7].

A list of women advised to make an appointment with their GP is sent to practices each month. Any women who have not booked a consultation or already consulted with a GP is contacted by practice staff and supported to book an appointment if they wish. Each patient contact and any reasons for not wishing to consult with a GP is recorded by the practice staff.

The process for returning results to participants and subsequent management is shown in Fig 2.

#### Training to support GPs.

The research team provides training to GPs within each participating practice to increase GPs’ knowledge and confidence around multifactorial breast cancer risk prediction and help them conduct consultations with women within the study. The training is composed of six educational videos developed by the CanRisk research team and further optional educational resources (training videos available on www.canrisk.org). The content covered in the educational videos was developed following a scoping review of the training needs of healthcare professionals in general practice and feedback from members of the CanRisk general practice expert advisory panel [20].

## Study outcomes and measures

The study aims to generate data on the following outcomes:

Uptake of multifactorial breast cancer risk assessment, including the proportion of those invited who consent and the proportion of those invited who complete the breast cancer risk assessment, with or without the inclusion of the polygenic risk score.Distribution of breast cancer risk, including the proportion of women who consent who are at moderate or high risk on the initial CanRisk assessment in general practice (with or without the PGS) and those at moderate or high-risk following assessment in secondary/tertiary care.Proportion of women at moderate or high risk of breast cancer. The proportion of registered women aged 40–48 years at the start of the study at participating practices who are at moderate or high risk of breast cancer after assessment in secondary/tertiary care will be compared with the proportion of women aged 40–48 years at moderate or high risk of breast cancer after referral to secondary/tertiary care at non-participating practices across Cambridgeshire and Peterborough during the same time period, and also compared with the proportion of registered women aged 40–48 years at participating practices in the 12 months prior to the study.Uptake of risk-reducing interventions, including the proportion of those at moderate or high risk who attend for a GP appointment, are referred to secondary/tertiary care, and take up enhanced screening and/or preventative medication.Completeness of risk factor information collected through MyCanRisk, including the presence of information completed for non-family history risk factors (e.g., height, weight, alcohol, women’s health) and the number of family members included in the pedigree.Change in psychological and behaviour measures (Table 2) following multifactorial breast cancer risk assessment at one month, three months, and six months after receiving the risk estimate.Acceptability of the pathway of proactive multifactorial risk assessment within general practice to women and GPs, including response rates and completion of questionnaires and the willingness for practices to take part.Costs and workload associated with delivery of proactive multifactorial risk assessment.

**Table 2 pone.0336902.t002:** Assessments.

Construct	Baseline	1 month	3 months	6 months

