
### Data collection

The data collection process is shown in Fig 2.

Participant baseline data is collected via an online questionnaire.

Participant level follow-up data is collected via participant questionnaires at 1, 3 and 6 months after receiving the results letter and from the GP electronic medical records 6 months after the last participant has received the results letter for all individuals who have consented to participate in the study. This includes coded entries relating to breast symptoms, breast cancer risk and, for those at moderate and high risk, uptake of risk-reducing interventions.

Practice-level aggregated data on the age, ethnicity and Index of Multiple Deprivation of all eligible women will be extracted at the end of the study from the GP electronic medical records. Practice-level and aggregated individual level data on the number of referrals of women potentially at above population-level risk for breast cancer and the outcomes of those referrals for all practices across Cambridgeshire and Peterborough for the period of the study will also be extracted from the electronic health records at the clinical genetics clinic at Cambridge University Hospitals NHS Foundation Trust. For the practices participating in this study, the same data will be extracted for the 12 months prior to the study. Data on the number of women registered at each practice will be extracted from publicly available National General Practice profiles.

A mixed-methods process evaluation is being conducted alongside collection of outcome data to explore how proactive breast cancer risk assessment is delivered and perceived at practice and patient levels. The main four questions guiding this element of the study will focus on: 1) whether this feasibility study did what it was set out to do; 2) whether the different elements in the study design worked and why; 3) what the different stakeholders thought about CanRisk and how it was implemented in general practice: and 4) whether implementing CanRisk in general practice is acceptable. Data is collected from women, GPs conducting breast cancer risk consultations, and practice managers and/or research leads from the different research sites. Three sources of data contribute to this process evaluation.

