#### Study status and timeline.

The study is currently at the stage of participant recruitment. Recruitment of participants to the study will run from 28 November 2024–30 June 2025, or until 1,000 women have been recruited. Data collection will continue for 6 months after the last recruited participant has received their risk estimate.

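### The before-after comparison of women identified sets an undefined study window against a fixed 12 months, and lets women already known to be at raised risk count as gains

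*Protocol article*

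**What the plan says.** Under Study outcomes and measures, the study-period quantity is "The proportion of registered women aged 40–48 years at the start of the study at participating practices who are at moderate or high risk" after secondary or tertiary assessment. It has two comparators: non-participating practices in the area over the same period, and the participating practices' own past, "also compared with the proportion of registered women aged 40–48 years at participating practices in the 12 months prior to the study".

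Data collection sets the extraction windows. Referrals and their outcomes "for all practices across Cambridgeshire and Peterborough for the period of the study will also be extracted" from the genetics clinic. For the historical comparator, "For the practices participating in this study, the same data will be extracted for the 12 months prior to the study".

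Study status and timeline gives the only dates: "Recruitment of participants to the study will run from 28 November 2024–30 June 2025, or until 1,000 women have been recruited", after which "Data collection will continue for 6 months after the last recruited participant has received their risk estimate".

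The exclusions under Participants cover a gene known in the family, a personal history of breast or ovarian cancer, a known germline variant, metastatic cancer or palliative registration, and dissent to research. An earlier moderate or high risk classification, or an earlier genetics assessment, is not among them. The section on risk categorisation offers referral to every woman found at moderate or high risk. The abstract states the purpose as finding women "who would otherwise not have been identified and so not had access to risk-reducing options".

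**The concern.** A cumulative proportion grows with the time over which cases are counted. If the study window is longer than the look-back, routine referrals alone produce an apparent increase; if it is shorter, they produce an apparent decrease. The protocol compares proportions, not rates, and fixes only one of the two windows.

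The second issue is what counts as identified. A one-off invitation to a whole age band also reaches women whose raised risk was recorded years ago. If they join, consult and are referred again, they enter the study numerator. The look-back year contains only that year's referrals, so women classified before it are absent from the comparator but present in the study count. They are not women who would otherwise have been missed.

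The difference in women identified is the direct evidence for the second question in the abstract and for the third listed objective. Errors of a few per 1,000 matter because the Sample size section quotes a precision of ±5 per 1,000 for this comparison.

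**Working it through.** **Inputs from the protocol.** Recruitment 28 November 2024 to 30 June 2025; follow-up 6 months after the last result; look-back 12 months; about 5,000 invited; 1,000 recruited; 17% (170) of those recruited above population risk; 80% of these attending the GP and being referred; stated 95% CI ±0.005.

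**Inputs assumed, because the protocol gives none.** Routine identification rate 1–10 per 1,000 women per year; result turnaround 0–6 months; already-known share 5–20%.

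**The plan's own figure.** The half-width for a difference of two proportions is 1.96 × √[p1(1−p1)/N + p2(1−p2)/N]. With N = 5,000, p1 = 170/5,000 = 0.034 and p2 ≈ 0, this is 0.0050. With p2 = 0.0025 and p1 = 136/5,000 + 0.0025 = 0.0297, it is 0.0049. The stated ±0.005 is therefore reproduced when the number registered is taken as the 5,000 invited.

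**Window length.** Recruitment is 214 days, and 214/30.44 = 7.0 months (Participant recruitment calls it 8). Full-course study window T = 7.0 + turnaround + 6. With no intervention effect, the spurious difference is r × (T/12 − 1), where r is the routine rate per year.

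| Turnaround (months) | T (months) | T/12 | Spurious difference at r = 5 per 1,000 |
|---|---|---|---|
| 0 | 13.0 | 1.09 | +0.4 per 1,000 |
| 2 | 15.0 | 1.25 | +1.3 |
| 4 | 17.0 | 1.42 | +2.1 |
| 6 | 19.0 | 1.59 | +2.9 |
| Recruitment only | 7.0 | 0.59 | −2.1 |

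Over the full-course windows, r = 1 per 1,000 gives +0.1 to +0.6, and r = 10 per 1,000 gives +0.9 to +5.9.

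**Already-known women.** Expected referrals: 0.80 × 170 = 136, and 136/5,000 = 27.2 per 1,000 invited. The 17% applies to women who consent, so no further completion factor belongs here. If a share q of the 136 was identified before the look-back year, the apparent gain includes q × 27.2 per 1,000 invited:

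- q = 5%: 1.4
- q = 10%: 2.7
- q = 20%: 5.4

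The stated half-width of 5 per 1,000 is reached at 25/136 = 18%. These are upper values for a given q, since some referred women may be reclassified downward on specialist assessment.

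**Uninvited women.** If 5,000 of 10,000 registered women are invited, the same 136 are 13.6 per 1,000 registered instead of 27.2. Uninvited women are in the denominators of both periods, so this dilutes the effect and adds no imbalance between periods.

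**The case against.** The best defence is that this is a non-randomised feasibility study, that none of the numerical progression criteria uses this comparison, and that exact extraction dates and a definition of newly identified could sit in an analysis plan not shown here. At a routine rate of 5 per 1,000 per year the window effect stays inside ±5 per 1,000. Known women count only if they join, consult and are referred again, and the records needed to separate them are largely being collected. All of this limits the importance. It does not remove the point: the protocol itself fixes the 12-month look-back, the study-period extraction and the numerator, and following them as written gives a biased difference.

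Some stronger readings are tempting but unsupported.

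- **Both comparisons have unequal windows.** They do not; the concurrent one is defined over the same period.
- **The study window can never be 12 months.** It can, because recruitment stops early if 1,000 is reached. For example, 4 months of recruitment plus 2 of turnaround plus 6 is 12. The window is undefined rather than necessarily different.
- **Uninvited women make the comparison unfair.** The protocol does allow that "either all or a random sample of those women who meet the eligibility criteria are invited to take part in the study", but the registered denominator is common to both periods. Scoring study yield per invited woman and routine care per registered woman would create the very mismatch it was meant to cure.

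**Conclusion.** The concern holds for two features of the comparison with the preceding 12 months. The windows are not tied to each other: on the protocol's dates a full recruitment run gives at least 13 months against 12. The resulting spurious increase is about 0.4–2.9 per 1,000 at an assumed routine rate of 5 per 1,000 per year and an assumed turnaround of up to 6 months; it changes sign if only recruitment counts. Separately, the numerator is not restricted to newly identified women, which adds about 2.7 per 1,000 invited for each 10% of the 136 expected referrals already known before the look-back. Women identified within the look-back and referred again count in both periods and do not inflate the difference. The numerator problem also reaches the concurrent comparison, because other practices make no such sweep.

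A reader might infer that the result must be inflated overall. The documents do not support that: the window effect can run either way, partial invitation dilutes the difference, and the routine rate, registered denominator and already-known share are not given. The net direction is unknown. The change is worth making before extraction, but does not threaten the feasibility aims.

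**What to change.** 1. **Windows.** Define the study window by start and end dates, and extract the look-back over the same number of months. Alternatively, express both periods per 1,000 woman-years. If rates are used, state the window length, because a one-off yield is averaged over it. The concurrent comparison needs no change.
2. **Numerator.** In every group and period, count only women with no earlier moderate or high risk classification or genetics assessment, and show re-identified women on a separate line. Apply the same source in all groups. Genetics-clinic records cover all practices, whereas coded GP entries are extracted only for consenting participants and can serve as a check there.
3. **Denominator.** Keep registered women aged 40–48 as the common denominator. Add the fraction invited at each practice and the yield per 1,000 invited as supplementary figures, not as a replacement.

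The cost is revised outcome and extraction wording plus one prior-assessment flag from records already in use. Because the clinic data are supplied in aggregate, the flag must be applied before aggregation. No new contact with participants is needed.
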